CGH is a 1,000-bedder acute care hospital with a consult-based PC team who also runs an outpatient PC clinic. SACH is a step-down care rehab and subacute facility that also houses a 24-bedder inpatient palliative ward and home care services. ViP is an integrated program involving specialists from CGH PC team and SACH home palliative supporting the SACH generalist home medical and home nursing services. The specialist team is a multidisciplinary team comprising of doctors, nurses, medical social workers and pastoral care trained in PC with input from other allied health professionals (physiotherapists, occupational therapists, speech therapists) while the generalist team are doctors and nurses trained in care of chronic illnesses with exposure to end of life care issues. Using a common electronic platform, the specialist team provides care for patient and families with more complex care needs, e.g. symptom control requiring frequent medication titration, subcutaneous medication infusion, unstable symptoms or high psychological needs requiring frequent touch points. The generalist team provides basic PC by engaging patient and family in advance care planning (ACP), education on the dying trajectory, managing non-complex symptoms, providing caregiving training and identifying patients with escalating PC needs requiring specialist intervention. The generalists have lesser touch points of between 3–6 months unless a regular nursing procedure is needed, e.g. change of nasogastric tube, indwelling urine catheter, wound dressing. As such, the specialists also provide ad-hoc rapid response service for patients managed by generalists when acute events occur. The program provides a 24 hours service. An on-call phone number is given on enrolment and patient/Next-of-Kin is briefed on the use of on-call service. On-call number is manned by a PC nurse or doctor with a PC consultant as 2^nd^ line support. Advice over the phone or urgent home visits are done depending on assessment of the situation by the on-call staff. Patients who have stable PC needs over a period of time have their care de-escalated to the generalist team till their care needs next peak.

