### Realist Evaluation

Realist evaluation (RE) is a more suitable approach for the evaluation of ViP. RE seeks to clarify implementation processes by providing a more explicit and in-depth understanding of the influence of existing and evolving contextual factors and mechanisms driving an intervention [24,25]. Furthermore, RE is able to accommodate inevitable changes surrounding intervention implemented in real-world settings.

The realist lens purports that an intervention is made of active theories that can only achieve successful outcomes if appropriate ideas are applied to the right context with appropriate social and cultural conditions [24]. The context–mechanism–outcome (CMO) configuration is used as the main structure for the evaluation to identify contextual factors (features of the conditions that influence the mechanisms of interventions) and mechanisms (what and how components of interventions result in changes) that are associated with variation in outcomes [24,25]. This study protocol documents an on-going RE of ViP using a mixed method approach. Table 1 describes the initial underpinning programme theories related to ViP.

**Table 1 T1:** Initial underpinning program theories.

IPT	IF	THEN	OUTCOME

1	If generalist nurses and doctors are trained with palliative care knowledge	Generalists will feel more confident in identifying cases and providing home PC	High acceptance, adoption and implementation fidelity of ViP

2	If advance care planning is conducted to support patients and caregivers in making informed decision related to care	Providers, patients and carers feel better prepared as there is an alignment for care at the end-of- life	High proportion of preferences honored at the end-of-life

3	If family carers are provided appropriate training and access to assistance to care for their loved ones at home	Carers will gain more confidence and feel more assured to provide care at home	Reduced caregiver burden and reduced acute hospital utilization

4	If a multidisciplinary team collaborate well through regular multidisciplinary meetings and open communication	Providers will work better with each other as they can trust each other to provide best care for patients and feel motivated to work towards a common goal of care	Adequate symptom management and appropriate coordination of services leading to reduced acute hospital utilization and healthcare cost

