### Phase 2: Testing of Program Theory using Empirical Data – 18 months

#### Study Design

A convergent parallel mixed methods study based on the triangulation design will be undertaken. Using the triangulation strategy, both quantitative and qualitative data will be collected concurrently. Data streams will be given equal weight and two datasets will be analyzed, compared and merged through iterative cycles of validation and confirmation of findings. Table 2 proposes a data framework which will be used to guide data collection according to the evaluation questions. Depending on the IPT elicited in phase 1, data framework will be revised accordingly.

**Table 2 T2:** Data Framework for Data Collection.

IPT	CONTEXT			MECHANISM				OUTCOME			
		
	INDICATORS	DATA SOURCE	MEASUREMENT MOMENT	INDICATORS	DATA SOURCE	MEASUREMENT MOMENT	SAMPLE SIZE	INDICATORS	DATA SOURCE	MEASUREMENT MOMENT	SAMPLE SIZE

1	No. of generalist nurses and doctors who are trained with palliative care knowledge	Administrative database	Quarterly for the first 2 years of the programme	Confidence of generalists who were trained and completed training for ViP	Interviews with healthcare providers	At least 6 months after program implementation	15/group	Perception among implementation stakeholders (providers and users) about the acceptability of the program	Interviews with healthcare providers & users	At least 6 months after program implementation	15/group

								Program acceptance rate (% of participants correctly identified in reference to all referrals)	Administrative database	Quarterly for the first 2 years of programme	Enrolees in year 1 and 2

								Dropout rate (% of eligible participants who were initially enrolled but withdrew from the programme)			

								Timeliness of care (% of patients with their palliative care commence within 2 days after when they are deemed to be “ready for care”)			

								Responsiveness to urgent needs (% of patients unstable for ≤ 3 days)			
			
2	% of enrolled patients with ACP reviewed or completed		Quarterly for the first 2 years of the programme	Patients’ and/or caregivers’ experience with ViP	Interviews with caregivers	At least 2 encounters with ViP team and <3 months after patient died		Concordance between documented treatment preference and actual treatment and place of death		At death	
	

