#### Data Collection

Context, mechanisms and relationships between context and outcomes, as defined in phase 1, will be tested through interviews with healthcare providers and users. As suggested by Manzano [29], questions to be asked in these interviews aim to ascertained how the program works, for whom, in what circumstances and how implementation has veered from what was initially planned. A purposive sample of 15 healthcare providers/managers and 15 healthcare users (patient and/or carers) per disease condition will be invited to take part in face-to-face or virtual interviews. The eventual sample size will be determined based on thematic saturation of the study. Data saturation is reached when the ability to obtain additional new information has been attained, and when further coding is no longer feasible [30].

In ensuring the quality of data collected, an interview guide will be used and interviewers will routinely reflect on interview experience and discuss data as they are being collected. Based on emerging understanding and identification of key knowledge gaps throughout the process of interviewing, interview questions will be revised accordingly.

Healthcare services utilization, health outcomes, healthcare cost and caregiver burden data will be collected and analyzed over time to evaluate intervention outcomes of ViP. A quasi-experimental design will be adopted by comparing the outcomes of the intervention group against a comparator group for healthcare utilization, outcomes and cost. Due to limited data available, a pre-post comparison will be made for caregiver burden. A quasi-experimental design is selected as it more truly mimics real-world constraints and provide a balance between internal and external validity [31]. Pragmatically, all patients who agree to participate, are accepted into the home-based PC service, utilized the services for at least one month and passed away as of December 2022 will be included as the intervention group. A retrospective comparator group will be identified from available CGH and SACH clinical databases. We plan to restrict the databases to within CGH and SACH for the identification of comparators. This is because patients are planned to be recruited from CGH and SACH in the first 2 years. This is a way of ensuring comparability between intervention and comparator group while keeping the data manageable.

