In identifying retrospective comparator group, relevant databases will initially be filtered for individuals who were referred to home hospice services between 2016–2019, have completed their advance care planning (ACP) and have died as of December 2020. Death status will be obtained from National Registry of Diseases Office records. Then, using a propensity matching strategy, a comparator group matched to intervention group in terms of age, gender, ethnicity, functional status, clinical status and re-admission characteristics will be identified. A ratio of 1:1 of intervention to comparator group will be used for matching.

In the assessment of healthcare utilization and health outcomes, date of death will be used as reference point for comparison. Acute hospital utilization (emergency department (ED) attendances, inpatient admissions, intensive care unit (ICU) admissions and length of stay (LOS)) will be extracted backwards from the date of death for 1 month (30 days), 3 months (90 days) and 6 months (180 days). Concordance of actualized place of death with preferences discussed as part of ACP will be determined after death as described by Tan et al [32].

We take a healthcare system perspective in examining the effect of ViP on healthcare cost. Development costs, program implementation costs and healthcare utilization costs will be measured. Development costs include costs incurred during the development of ViP. The program implementation costs consider costs related to the implementation of the program including the manpower, travel, equipment, materials used for patient and caregiver training and costs associated with multidisciplinary team meetings. The development and implementation costs will be systematically collected using the WHO’s CostIt instrument [33] and will be divided by the number of clients enrolled into the program to obtain per patient cost. Healthcare utilization cost for the use of hospital inpatient and outpatient services and primary care services in the metrics of full gross bill amounts will be extracted for six-month period before death.

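### Completed advance care planning is required of comparators but not of ViP patients, so the utilisation, health-outcome and cost contrast selects one arm only on a component of the programme

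*Protocol article*

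**What the plan says.** **Comparators** (Protocol article, Phase 2, Data Collection). The databases are first filtered to people referred to home hospice in 2016–2019 who "have completed their advance care planning (ACP) and have died as of December 2020". Propensity matching at 1:1 follows, on demographic, functional, clinical and re-admission characteristics. ACP status is not among the matching variables.

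**ViP group** (same section). Patients who agree, are accepted, "utilized the services for at least one month and passed away as of December 2022 will be included as the intervention group". No ACP condition appears.

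**ACP as part of ViP.** The Intervention section describes it as delivered by the programme: "The generalist team provides basic PC by engaging patient and family in advance care planning (ACP". In Table 1 it is the starting condition of programme theory 2: "If advance care planning is conducted to support patients and caregivers in making informed decision related to care". Table 2 lists, as a context indicator followed quarterly, the percentage "of enrolled patients with ACP reviewed or completed". An indicator expressed as a share does not presume 100%.

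**Outcomes.** The same comparator group serves utilisation, health outcomes and cost. One outcome does need an ACP record: "Concordance of actualized place of death with preferences discussed as part of ACP will be determined after death".

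**The concern.** A comparator group should show what would have happened without the programme. Here every comparator already has one element that the programme supplies, while ViP patients may or may not have it. Two things follow for utilisation, health outcomes and cost.

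- Even if every ViP patient completed ACP, the contrast would estimate only what the other components of ViP add. The second research question asks whether ViP as a whole achieves its intended outcomes.
- If some ViP patients do not complete ACP, the arms also differ on ACP itself, with the comparators having more of it.

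The planned adjustment does not help. A ViP patient without ACP has no comparator of like status. A regression could separate ACP from group only by borrowing the ACP effect entirely from ViP patients. This is the only between-group comparison planned for effectiveness and cost, so the estimate most likely to be read as the effect of ViP is the one affected.

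**Working it through.** The article gives no ACP rate, ACP effect, effect size or sample size for the matched comparison, so there is no stated figure to reproduce. Every input below is an assumption, used to show what the filter can do.

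**Inputs**
- r: rate ratio of acute use, ACP versus no ACP (0.7 to 1.1)
- p0: share with ACP in an unfiltered comparator pool (0.2 to 0.8)
- pV: share with ACP among ViP patients
- θ: effect of the other ViP components (0.85)

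**Formulas**, with the rate without ACP set to 1
- Unfiltered ratio = θ(1 − pV(1 − r)) / (1 − p0(1 − r))
- Ratio with ACP required of comparators only = θ(1 − pV(1 − r)) / r
- Distortion from the filter = second ÷ first = (1 − p0(1 − r)) / r; θ and pV cancel

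**Example:** r = 0.8, p0 = 0.5, pV = 0.8, θ = 0.85
- ViP rate: 0.85 × (1 − 0.8 × 0.2) = 0.714
- Unfiltered: 0.714 / 0.9 = 0.79
- ACP required of comparators only: 0.714 / 0.8 = 0.89
- ACP required in both arms: 0.85, the effect of the other components alone
- Distortion: 0.9 / 0.8 = 1.125

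**Distortion over the range** (above 1 is against ViP)

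| r | p0 = 0.2 | p0 = 0.5 | p0 = 0.8 |
|---|---|---|---|
| 0.7 | 1.343 | 1.214 | 1.086 |
| 0.8 | 1.200 | 1.125 | 1.050 |
| 0.9 | 1.089 | 1.056 | 1.022 |
| 1.0 | 1.000 | 1.000 | 1.000 |
| 1.1 | 0.927 | 0.955 | 0.982 |

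**Adding selection.** Let s be the rate ratio of ACP completers to non-completers for reasons other than ACP itself. Then distortion = ((1 − p0) + p0·r·s) / (r·s). It exceeds 1 only when r·s is below 1. At p0 = 0.5:

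| r | s = 1.0 | s = 1.1 | s = 1.25 | s = 1.4 |
|---|---|---|---|---|
| 0.8 | 1.125 | 1.068 | 1.000 | 0.946 |
| 0.9 | 1.056 | 1.005 | 0.944 | 0.897 |
| 1.0 | 1.000 | 0.955 | 0.900 | 0.857 |

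The filter therefore works against ViP when ACP lowers acute use and completers are not otherwise heavier users. It has no effect, or the opposite one, in other parts of a plausible range.

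**The case against.** **Direction.** A reader might infer that the filter biases utilisation and cost against ViP. The documents do not support that as a fact. Table 1 ties ACP to "High proportion of preferences honored at the end-of-life". It ties "Reduced caregiver burden and reduced acute hospital utilization" to carer training and access to assistance (theory 3), and utilisation and cost to team collaboration (theory 4). Table 2 does expect documented preferences to bear on the treatment actually given, which makes an ACP effect on acute use plausible, but no size or sign is stated. Other asymmetries, such as the one-month service rule for ViP only and the earlier calendar period of the comparators, also act on the net bias.

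**Programme theory 2.** A reader might also infer that this theory becomes untestable, or that ACP completion is a measured result of ViP. Neither holds. Completion is a context indicator in Table 2. The outcome of the theory is preferences honoured, which concordance, the quarterly ACP shares and the caregiver interviews can still examine. What is lost is narrower: the between-group contrast cannot test the starting condition, because all comparators meet it.

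**A reason for the filter.** Concordance needs a recorded preference, so an ACP requirement is defensible for that outcome. Requiring ACP may also pick out comparators as engaged with end-of-life planning as ViP patients, who signed a service agreement and stayed at least a month, whereas comparators were only referred. Both arguments have weight. The first covers one outcome only and would call for the same restriction in the ViP group. The second supports a sensitivity analysis. ViP against people who all have ACP is a legitimate contrast, but a narrower one than the research question.

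**Condensed article.** The full protocol may give the reason for the filter, the regression covariates and the sensitivity analyses. The filter itself, however, is stated outright and applied to the comparator group as a whole.

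**Conclusion.** The point holds as a one-sided selection rule. ACP is required of comparators, not required of ViP patients, not matched on, and is part of the programme. Any contribution of ACP to utilisation, health outcomes or cost is wholly or partly taken out of the estimated effect of ViP.

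Size and sign rest on assumptions. With a 10–30% reduction in acute use from ACP, 20–80% ACP in an unfiltered pool and no selection of completers, the rate ratio is inflated by a factor of 1.02 to 1.34. With no ACP effect and no selection the factor is 1.00. With completers 25% heavier users for other reasons and 50% ACP in the pool, it is 1.00 at r = 0.8 and 0.94 at r = 0.9. The net direction across all differences between the arms cannot be stated from the documents.

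**What to change.** For utilisation, health outcomes and cost:
- Remove ACP completion from the comparator filter.
- Report ACP status in both groups.
- If prior ACP is regarded as a confounder, match both groups on ACP completed before a defined index date, for example referral for comparators and enrolment for ViP. The article anchors outcomes on date of death and states no index date, so this has to be written in.
- Keep the ACP-filtered comparison as a sensitivity analysis, described as such.

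For concordance only, restrict both groups equally to patients with a documented preference.

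**Cost.** One filter changes in existing databases, and the comparator pool grows. There will be two matched sets to describe, and an index date to define if prior ACP is matched on. Comparators may be less like ViP patients in their engagement with end-of-life planning; the retained sensitivity analysis addresses that.

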**Figure 1 F1:**
[figure not shown]
Recruitment workflow of ViP.

After enrolment, care is then stratified according to needs based on Palliative Care Outcomes Collaboration (PCOC) assessment [21]. Patients of higher acuity or requiring closer monitoring will be cared for by the specialists. Patients deemed more stable will be serviced by the generalists with ad-hoc visits by the specialists to manage acute deteriorations. For every patient enrolled, an individualized care plan is developed, revisited regularly and executed collaboratively by healthcare providers and patients/carers. Patients are contacted at least once a month via phone call, video call or home visit. Frequency of contact is guided by PCOC assessment at each contact. Weekly multidisciplinary team meetings are held to discuss new, complex cases and to review mortalities as a formal debrief and to identify bereavement needs. Allied health, community-based service providers or lay extenders are engaged to provide an additional layer of support for patient or caregiver depending on patient/carers’ needs. Service is provided from enrolment until (i) the patient passes away and bereavement support is no longer required, (ii) patient’s condition improves and/or stabilizes such that the patient is no longer deemed to suffer from a terminal illness and home PC support is not required, (iii) patient is admitted to an inpatient hospice for terminal care or admitted to the acute hospital for more than three months, (iv) patient or family requests to withdraw from the service and (v) patient moves out of the zone of coverage.

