### Problem Statement

ViP recruited its first patient in December 2020 and is in its infancy. While the general program design, processes and guiding principles were drafted by the ViP team with inputs from policy makers, it is not well understood “for whom” the planned program will be suitable and “how” ViP will work and be sustainable in the local context. To the best of our knowledge, ViP is one of the first integrated home PC model for non-cancer patients in Singapore involving an acute hospital, home medical and nursing teams and an inpatient hospice hence there are limited relevant context-specific insights from which ViP can learn from. As such, a rigorous and practical evaluation strategy to address the existing knowledge gaps is warranted. Findings from such evaluation will provide insights to support the implementation and further development of ViP and similar programs in Singapore and beyond.

Commonly used evaluation design, Randomised Controlled trial (RCT) design, which focuses solely on outcomes evaluation is rigid when evaluating a complex intervention. It is unsuitable for evolving interventions and rarely adequately or even explicitly address the context-specific drivers behind any outcomes and their relationship to the underlying program theory [22]. This makes it difficult to interpret their findings for improvement purposes due to its limited relevance in reality. [23].

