3	% of needy patients who were provided support	Administrative database & interviews with caregivers	Quarterly for the first 2 years of the programme					Change in caregiver burden score before and after intervention	Zarit Burden Interview-12	Baseline (at enrolment) and every 3 months after enrolmentuntil patients’ death	

								No. of ED attendances, in-patient admission and length of stay (LOS)	Administrative databases	1 month (30 days), 3 months (90 days) and 6 months (180 days) prior to death	

								% of patients with good management of symptoms	PCOC – symptoms assessment		
	
4	% of cases discussed in the MDM (multidisciplinary meetings)	Administrative database		Providers’ working experience	Interviews with providers	At least 6 months after program implementation		Development costs, program implementation costs and healthcare utilization costs	Administrative database	6 months prior to death	
		
	Quality of collaborative and communications between providers	Interviews with providers						Average duration in each PCOC stage		1 month (30 days), 3 months (90 days) and 6 months (180 days) prior to death	
	
5	Implementation experience	Interviews with providers	At least 6 months after program implementation					Perceived quality of care	Mortality follow-back survey	≤3 months after death	
	
*6*	Extent of support from management							Sustainability	Clinical Sustainability Assessment Tool (CSAT)	At least 6 months after program implementation	

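### Hospice and palliative-ward days are not among the listed utilisation or cost items, so unequal hospice use between groups could be credited to care at home or look like a saving

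*Protocol article*

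**What the plan says.** The Data Collection section defines the utilisation outcome by its components: "Acute hospital utilization (emergency department (ED) attendances, inpatient admissions, intensive care unit (ICU) admissions and length of stay (LOS)) will be extracted backwards". The count starts at death and covers three windows (30, 90 and 180 days). The optional merge with Ministry of Health data, described in the same section, also brings in acute use only. Utilisation cost covers hospital inpatient, hospital outpatient and primary care bills in the six months before death, under a healthcare system perspective. Neither list names hospice, and no outcome row of Table 2 contains hospice or palliative-ward days.

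The hospice is nevertheless part of the programme. On the partner hospital, the intervention section says: "SACH is a step-down care rehab and subacute facility that also houses a 24-bedder inpatient palliative ward and home care services". The Problem Statement describes a model "involving an acute hospital, home medical and nursing teams and an inpatient hospice". One listed reason for service to end is that the "patient is admitted to an inpatient hospice for terminal care or admitted to the acute hospital for more than three months".

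The intervention group consists of consenting patients who used the service for at least one month and had died by December 2022. Leaving ViP for a hospice bed does not remove a patient from it. Comparators come from CGH and SACH databases. They were referred to home hospice services in 2016–2019, had completed advance care planning, and had died by December 2020.

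**The concern.** Because the windows run backwards from death, they include any days after home service ended. A ViP patient who spends the last days of life in a hospice or palliative bed is largely out of reach of ED attendance, acute admission and ICU on those days, and the days themselves are counted nowhere.

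Fewer acute days can therefore arise in two ways: patients were supported at home, or they were in another institutional bed. The listed utilisation outcomes look the same in both cases. This matters in a realist evaluation, where the mechanism is itself a result. Table 1 credits lower acute use to carers' confidence in caring at home (IPT 3), and lower acute use and cost to teamwork (IPT 4). Research question 5 asks how ViP works.

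The cost comparison has the same gap. If acute bills fall because hospice bills replace them and the latter are not collected, a shift of cost within the healthcare system appears as a saving.

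**Working it through.** The plan states no hospice-use rate, sample size or effect size for this comparison, so there is no figure of its own to reproduce. The calculations below are illustrations; every input except the window lengths is assumed.

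**1. Time at risk removed.** Let p be the share of ViP patients who use a hospice or palliative bed before death, d the days each spends there, and W the window. With no hospice use among comparators, the share of group time at risk of acute use that is lost is p × d / W.

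| Assumed p and d | p × d | W = 30 | W = 90 | W = 180 |
|---|---|---|---|---|
| 10%, 7 days | 0.7 days | 2.3% | 0.8% | 0.4% |
| 20%, 14 days | 2.8 days | 9.3% | 3.1% | 1.6% |
| 40%, 21 days | 8.4 days | 28.0% | 9.3% | 4.7% |

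If comparators also use such beds, what counts is the difference in p × d between the groups. If p × d is equal, the result is 0% in every window.

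**2. Apparent reduction in acute bed-days.** Let s be the excess share of ViP patients moved to a hospice bed relative to comparators, h the acute days replaced per moved patient, and B the comparators' mean acute bed-days in the last 30 days. With no effect on total bed-days, the relative reduction in acute days is s × h / B. Taking h = 7 or 14 and B = 8 or 12:

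| s | Lowest (h = 7, B = 12) | Highest (h = 14, B = 8) |
|---|---|---|
| 0 points | 0% | 0% |
| 5 points | 2.9% | 8.8% |
| 10 points | 5.8% | 17.5% |
| 20 points | 11.7% | 35.0% |

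**3. What would tell the two explanations apart.** Take B = 8, s = 20 points, h = 7, so 0.20 × 7 = 1.4 acute days are avoided per patient (1.4 / 8 = 17.5%). For simplicity, comparators have no hospice days and no other institutional stay.

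| Last 30 days, mean per patient | Acute | Hospice | Total institutional | At home |
|---|---|---|---|---|
| Comparator | 8.0 | 0 | 8.0 | 22.0 |
| ViP, bed substitution | 6.6 | 1.4 | 8.0 | 22.0 |
| ViP, kept at home | 6.6 | 0 | 6.6 | 23.4 |

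The acute column is identical in the two ViP rows. Only total institutional days and days at home separate them.

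**The case against.** The strongest defence is that acute use is the right outcome for the stated purpose. Reducing unnecessary acute use is the programme's first aim, and IPT 3 and IPT 4 name it as their outcome. The hospice belongs to the integrated model, so timely transfer may be one of ViP's own mechanisms, and keeping transferred patients in the group avoids selecting on how service ended. All of this stands. A reader might infer that a fall in acute use would be an artefact; it would not. Only its attribution to care at home, and any claim of system saving, are exposed.

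A reader might also infer that misattribution is bound to happen. The documents do not support that. Comparators were themselves referred to home hospice and come from the same two institutions, so they may have used the same beds. Equal use cannot be presumed either: comparators needed only a referral, before ViP existed, while ViP patients must have used at least a month of a service run jointly with the hospital that houses the ward. Matching on baseline characteristics does not balance hospice use that comes later.

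A third tempting reading is that the study cannot tell home deaths from hospice deaths. It can, because actual place of death is determined for concordance with care preferences. But place of death gives no count of days. Interviews and triangulation also address how ViP works, though they do not measure days spent in each setting.

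Finally, the article is condensed, the data framework may be revised after Phase 1, and sensitivity analyses are not itemised. Even so, it does list the components of utilisation and cost. Table 2 refers to inpatient admission without the word acute, and a SACH palliative-ward stay might count as hospital inpatient cost. The text settles neither.

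**Conclusion.** The point holds as a conditional one. As listed, the utilisation and cost items cannot show whether fewer acute days were matched by more days at home or by more days in a hospice or palliative bed. If hospice use is higher in ViP than among comparators, a real fall in acute use could be wrongly credited to IPT 3 and IPT 4, and substitution could look like a saving.

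The size is unknown. It is zero with equal use. In the middle illustrative case (20% of patients, 14 days, no comparator hospice use) it is 9.3% of time at risk at 30 days, falling to 3.1% and 1.6% in the longer windows. The shortest window is therefore the most exposed. The acute-use outcome remains valid for the programme's stated aim. The gap is worth closing before data extraction because it limits what can be concluded about mechanism and cost.

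**What to change.** - Keep acute hospital use as the outcome for the stated aim.
- Extract inpatient hospice and palliative-ward admissions and days for both groups over the same 30-, 90- and 180-day windows.
- Report total institutional days and days at home beside acute use, as secondary outcomes.
- State whether a SACH palliative-ward stay counts as an inpatient admission, and align Table 2 with the Data Collection text.
- Include hospice and palliative-ward bills in utilisation cost, or state that they are excluded and limit the cost claim accordingly.
- Attribute a reduction in acute use to home care only if days at home are also higher than among comparators.

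The cost is modest but more than one extra field. SACH databases are already used to identify comparators, but outcome data come from eHints, which covers SingHealth institutions and is not said to hold SACH ward stays, so a separate SACH extract may be needed. Stays in other hospices may be incompletely captured, possibly to a different degree in the two groups; this should be stated as a limitation.
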